**Sample size estimate.**

Based on the cumulated incidence endpoint and study hypothesis that shortening time to detection of MRSA carriage by 3 days will reduce MRSA nosocomial acquisition by 50%, a standard sample size calculation for detecting a difference in proportion between 3% and 1.5% in two independent samples with α=0.05 and ß=0.20 (80 % power) suggests that 1,237 patients should be included in each study arm. Assuming non-independence of samples due to the time dependence of MRSA transmission rates between study phases and taking into account the cluster design, a conservative 150 % sample size estimate would suggest enrollment of 1850 patients per arm in each hospital, or a total inclusion of 7,400 patients.

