## Study design

**Study type and patient population**

The study will be an open label, **cluster randomized intervention trial,** with **cross-over design.** It will be carried out in parallel over a one year period in two large hospitals in

1. patients admitted to high risk surgical, medical and geriatric wards of Erasme hospital (7 to 8 wards)
2. patients admitted to the intensive care departments, medical and geriatric wards of AZ St Jan hospital (6 to 7 ward).

The Erasme hospital is an 858-beds academic hospital located in Brussels, including medical and surgical care departments. The AZ-St Jan hospital is an 800-bed general teaching hospital located in Brugge, including medical and surgical care departments. Both institutions have an integrated MRSA surveillance and control program in place for over 10 years. These programs adhere to the national recommendations for MRSA control in acute care hospitals (BICS-CSH/HGR 2003). These include: active screening of MRSA carriers on admission by selective culture of nasal, throat and wound sites in high risk patients and/or units, flagging of previously detected MRSA carrier patients at re-admission, placement of MRSA carriers in single room with contact isolation precautions and decolonisation therapy of carriers with nasal mupirocin and antiseptic bathing for 5 days.

The choice of a minimum size of effect of 50% reduction in MRSA acquisition is based on the assumption that a 6-fold reduction of transmission rate can be expected from placing MRSA positive patients in isolation, and that the reduction from 3 to 0 days of unisolated stay can be expected by the intervention. Assuming a baseline rate of 3% nosocomial acquisition rate in the exposed population of study wards, the study population will include 3,700 patients in each hospital with approximately 50 new cases of MRSA acquisition in the control arm (n= 1,850 patients) versus 25 new cases in the intervention arm (n= 1,850 patients).

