The **primary analysis** will be based on Poisson regression two level model (individual patient and unit exposure) performed at each hospital level to assess the impact of the intervention on local incidence-density of MRSA nosocomial colonisation, and ajusted for four potentially confounding factors. The dependent variable will be endpoint 1 above. The ward level **independent variables** will include (1) **intervention arm**, (2) MRSA **colonisation pressure** (as determined by monthly proportion of MRSA colonisation-days/total patient-days among patients admitted during the preceding month in one particular ward), (3) **staff** **compliance with standard and isolation precautions** (as determined by a sample of 50 observations per ward/ trial period, including 25 care opportunities for patients under MRSA isolation precautions and 25 for patients cared for with standard precautions; see appendix 6 for precautions compliance monitoring procedure) (4) **antibiotic use** (as determined by cumulated number of Defined Daily Doses of J01 ATC class of antimicrobial drugs per monthly period) and (5) monthly bed occupancy rate.

Heterogeneity of effect by ward/hospital will be assessed. **To quantify the protective efficacy of the intervention** for the at risk population per centre, the adjusted Rate Ratio (and 95% confidence interval) of nosocomial MRSA acquisition will be calculated for the intervention arm in all study wards per hospital. Pooled analysis of average effect for both hospitals will be calculated. In case of significant heterogeneity between hospitals, hospital level will be added as covariate in the model.

**Secondary analyses** will include:

A. Logistic regression two level models (individual patient and unit exposure) will be performed at each hospital level to assess the impact of the intervention on local cumulated incidence of MRSA nosocomial colonisation. The dependent variable will be endpoint 6 above. The **independent variables** will include patient age, sex and the 5 independent ward level indicators as described above for the primary Poisson analysis.

Heterogeneity of effect by ward/hospital will be assessed. Pooled analysis of average effect for both hospitals will be calculated. In case of significant heterogeneity between hospitals, hospital level will be added as covariate in the model.

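### The 1,237 per arm gives 80% power only with a one-sided 5% test that the protocol never declares; two-sided it gives about 71%, and the pooled power claim in Addendum 1 has the same gap

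*Protocol*

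**What the plan says.** The section on sample size works from the cumulative incidence endpoint and describes "a standard sample size calculation for detecting a difference in proportion". Its inputs are "detecting a difference in proportion between 3% and 1.5% in two independent samples", α=0.05 and β=0.20, and it "suggests that 1,237 patients should be included in each study arm". It does not say whether α is one-sided or two-sided.

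To allow for clustering and time dependence, the section then says that "a conservative 150 % sample size estimate would suggest enrollment of 1850 patients per arm in each hospital", which makes 7,400 patients in total. The same 1,850 per arm per hospital appears under Study type and patient population.

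The primary analysis, under Study endpoints and statistical analysis, is a two-level Poisson model. From it, "the adjusted Rate Ratio (and 95% confidence interval) of nosocomial MRSA acquisition will be calculated".

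Addendum 1 reports a baseline acquisition incidence of 0.79% (95% CI 0.34% to 1.55%) and makes the result for both hospitals combined the primary endpoint. It states that, at the upper confidence limit, the planned sample size still gives 80% power for a 50% reduction with a possible cluster effect included. It gives neither an inflation factor nor the sidedness of the test.

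**The concern.** An unqualified α=0.05 in a calculation called standard, alongside a 95% confidence interval, is normally read as a two-sided 5% test. On that reading 1,237 per arm is too few for 3% versus 1.5% with 80% power.

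The shortfall does not stop at the base figure. The factor of 1.5 is the plan's only allowance for clustering and for dependence between periods, and it is applied to a base that is already low. If the factor is needed, the risk of missing a true halving of acquisition is about 29% rather than the stated 20%. Because the current primary comparison is the pooled one in Addendum 1, it matters whether the 80% stated there depends on the same undeclared choice.

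**Working it through.** **Inputs.** From the sample size section: p1 = 0.03, p2 = 0.015, α = 0.05, power 80%, inflation 1.5. Allocation is 1:1. From Addendum 1: p1 = 0.0155 and its half, p2 = 0.00775. The pooled arm is 2 × 1,850 = 3,700.

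**Formula.** With p̄ = (p1 + p2)/2,

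n per arm = [z_α·√(2p̄(1−p̄)) + z_β·√(p1(1−p1) + p2(1−p2))]² / (p1 − p2)²,

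where z_β = 0.8416, and z_α = 1.6449 one-sided or 1.9600 two-sided.

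**Step 1: reproduce the plan's figure.** For 3% versus 1.5%, √(2p̄(1−p̄)) = 0.20973 and the second root is 0.20946.

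- One-sided: (1.6449 × 0.20973 + 0.8416 × 0.20946)² / 0.015² = (0.34498 + 0.17629)² / 0.000225 = 1,208.
- Two-sided: (0.41107 + 0.17629)² / 0.000225 = 1,534 (rounded up).

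Other versions of the formula give:

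| Method | One-sided | Two-sided |
| --- | --- | --- |
| Pooled variance | 1,208 | 1,534 |
| Unpooled variance | 1,206 | 1,531 |
| Arcsine | 1,175 | 1,491 |
| Log odds ratio | 1,257 | 1,596 |
| Log risk ratio | 1,261 | 1,601 |
| Continuity-corrected | 1,338 | 1,664 |

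The stated 1,237 lies within the one-sided range and 2.4% above the usual one-sided value. The smallest two-sided value is 1,491.

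**Step 2: power at the stated sizes, 3% versus 1.5%.** Power = Φ{[(p1 − p2)√n − z_α·√(2p̄(1−p̄))] / √(p1(1−p1) + p2(1−p2))}.

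- n = 1,237, two-sided: Φ(0.556) = 71.1%. One-sided: Φ(0.872) = 80.8%. Exact enumeration of the two-sided chi-square test gives 72.2%.
- n = 1,850 with inflation 1.5 (effective 1,850/1.5 = 1,233), two-sided: 71.0%.
- n = 1,850 with no inflation, two-sided: 86.8%.
- Largest inflation that keeps 80% two-sided: 1,850/1,534 = 1.21.
- Size needed for 80% two-sided with the full 1.5: 1,534 × 1.5 = 2,301 per arm per hospital.

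**Step 3: Addendum 1, pooled, 1.55% versus 0.775%.** The addendum names no factor, so 1.5 is carried over as an assumption.

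| | One-sided 5% | Two-sided 5% |
| --- | --- | --- |
| n per arm before inflation | 2,365 | 3,002 |
| × 1.5 | 3,548 | 4,503 |
| Against 3,700 available | enough | not enough |
| Power, 3,700 with inflation 1.5 | 81.5% | 71.9% |
| Power, 3,700 with no inflation | 92.9% | 87.5% |

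The largest inflation that keeps 80% two-sided is 3,700/3,002 = 1.23. The addendum's claim holds one-sided with the 1.5 factor and fails two-sided with it.

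**The case against.** **It may be no miscalculation.** The aim is directional (a reduction of at least 50%), sidedness is unstated, and a one-sided 5% formula comes close to 1,237. This stands. A reader might infer a plain arithmetic slip, but the documents do not show one. They show a base that fits a one-sided test which is nowhere declared and which does not match the reported 95% interval. The directional hypothesis in the time-series analysis is secondary and sets no one-sided α.

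**71% is not the power of the trial.** This also stands. No comparison enrols 1,237 independent patients per arm. The protocol gives no intracluster or between-period correlation, so the true design effect is unknown. The 71% applies to 1,850 only if inflation really is 1.5.

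**How much of the allowance is lost.** It is tempting to say most of it, but that depends on the measure. In patients it is (1,534 − 1,237)/(1,850 − 1,237) = 297/613 = 48%. As a share of the excess ratio it is (1.50 − 1.21)/0.50 = 58%.

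**The per-hospital basis is superseded.** True: the pooled result is now primary, and at 3% versus 1.5% the pooled 3,700 with inflation 1.5 would have about 94% two-sided power. But Addendum 1 replaces 3% by at most 1.55%, and there the same gap returns.

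**Incidence matters more than sidedness.** At the observed 0.79%, pooled power with inflation 1.5 is about 44% two-sided and 56% one-sided. That larger loss is a separate matter. It does not make the 80% stated at the upper limit correct.

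**Conclusion.** The concern holds as a mismatch between the sample size and the inference planned. With two-sided α=0.05, the stated 80% is not delivered by the base figure (71%), nor by 1,850 per arm per hospital or the pooled 3,700 if an inflation of 1.5 is needed (71% and 72%). Both planned sizes reach 80% two-sided only if inflation is no more than 1.21 and 1.23 respectively. So 1,850 is about 121% of the two-sided base, not 150%.

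This rests on reading the 95% confidence interval as two-sided 5% inference and, for Addendum 1, on carrying over the 1.5 factor. Whether an allowance of about 1.2 is enough cannot be judged from the protocol.

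**What to change.** - State that the test is two-sided at α=0.05, in line with the 95% confidence interval.
- In the sample size section, replace 1,237 by about 1,534 per arm. State that 1,850 per arm per hospital gives about 71% power with an inflation of 1.5, 80% with at most 1.21, and 87% with none.
- Stop describing 1,850 as a conservative 150% estimate.
- In Addendum 1, name the inflation factor and restate the pooled power at 1.55% versus 0.775%: about 72% with 1.5, or 80% with at most 1.23.

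The cost is a change of wording and a less favourable stated power. The planned number of patients does not change.

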**Secondary endpoints**

These will include three related process of care indicators:

1. Time (h) between admission and notification of MRSA positive culture/PCR
2. Time (h) between admission and placement of newly detected MRSA carrier in contact isolation

Secondary endpoints will also include the following microbiologically-documented outcomes:

1. Number of patient-days of MRSA positive patients cared for with standard precautions and not isolated
2. Cumulative incidence of MRSA nosocomial colonisation, defined as number of new cases of hospital-acquired MRSA (first positive culture >48 h after admission) divided by the number of admitted patients who stayed ≥ 3 days and were MRSA negative on admission by culture and PCR testing, if performed.
3. Cumulative incidence of MRSA nosocomial infection, defined as number of new cases of hospital acquired MRSA infection (according to CDC definitions for nosocomial infection and with first MRSA positive culture > 48 h after admission) divided by number of admitted patients who stayed ≥ 3 days.
4. Number of clusters of ≥ 2 cases/unit of acquired MRSA colonisation with a clonally related strain, defined as a MRSA strain with the same spa type or PFGE major type.
5. Sensitivity and specificity of rapid PCR test compared to conventional culture for MRSA screening, taking into account one parallel set of admission nasal screening samples per patient.

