C. The median process time intervals (endpoints 2-4 above) and number of missed isolation days (endpoint 5 above) will be compared by Wilcoxon tests for patients within the same unit/hospital between arms; median times (interquartile range) will be compared for each study phase and hospital.

D. In addition, monthly rates of endpoints 1, 6 and 7 will be plotted over time and interrupted time-series, segmented linear regression analysis of temporal trends per study periods will be performed for each hospital. The hypothesis to be tested is that there will be a significant drop in the level of rates from the beginning of the intervention compared to the baseline or control period, possibly associated with a negative change of slope due to a decreasing trend in the intervention period.

E. Diagnostic accuracy (clinical sensitivity and specificity) will be calculated for the rapid PCR test (MRSA GeneXpert, Cepheid) compared to conventional culture as gold standard based on all matched nasal swabs (N=3,700) tested in parallel during the 10 month trial period.

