**Budget V4: to be adjusted for number of PCR tests needed**

| **Personnel** | **N** | **Cost/unit** | **Cost in €** |
| --- | --- | --- | --- |
| Infection control nurse | 24 MM | 50,000/yr | 100,000 |
| Laboratory technologist | 4 MM | 45,000/yr | 15,000 |
| Microbiologist | 2 MM | 70,000/yr | 11,500 |
| **Working costs** |  |  |  |
| Xpert PCR System | 1 | 50,000 | -* |
| Xpert-MRSA test | 1300 to 1850 | 48 | -* |
| Surveillance cultures |  |  |  |
| Admission | 7,400 | 4 | -** |
| Hospital stay/discharge | 15,000 | 4 | 60,000 |
| Molecular typing MRSA | 200 | 15 | 3,000 |
| Data analysis |  |  | 5,000 |
| **Total** |  |  | 194,500 |
| Overhead 15 % |  |  | 29,175 |
| **Grand total (2 hospitals)** |  |  | **223,675** |

* the estimated number of PCR tests is based on the proportion (35 to 50 %) of admitted study patients fulfilling the screening test indication criteria. Test kits (n=600) are to be provided free of charge by Cepheid. Additional kits to be purchased.

** charged to hospital budget (routine MRSA surveillance cultures)

#####

Reference List

(3) Verbrugh HA. Value of screening and isolation for control of methicillin-resistant Staphylococcus aureus. Clin Infect Dis 2005; 41(2):268-269.

(4) Struelens MJ. Rapid identification of methicillin-resistant Staphylococcus aureus (MRSA) and patient management. Clin Microbiol Infect 2006; 12 Suppl 9:23-26.

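### The 1,850 per arm per hospital (3,700 and 7,400) serves both as the at-risk denominator for power and as the count of all screened admissions, with nothing linking the two

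*Protocol*

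**What the plan says.** **Sizing.** The Protocol's *Sample size estimate* opens "Based on the cumulated incidence endpoint and study hypothesis". It sets the target as "detecting a difference in proportion between 3% and 1.5" per cent, "in two independent samples with α=0.05 and ß=0.20 (80 % power"), and "suggests that 1,237 patients should be included in each study arm". A 150% factor, attributed to time dependence between phases and to the cluster design, leads to "enrollment of 1850 patients per arm in each hospital, or a total inclusion of 7,400 patients".

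**Denominator.** Under *Secondary endpoints*, cumulative incidence is the number of new cases "divided by the number of admitted patients who stayed ≥ 3 days and were MRSA negative on admission by culture and PCR testing", if PCR was done. The primary incidence density (*Study endpoints and statistical analysis*) uses patient-days from the same restricted group.

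**The same totals as screening counts.** Secondary analysis E estimates PCR accuracy "based on all matched nasal swabs (N=3,700"), which is 2 × 1,850, the whole PCR arm over both hospitals. *Budget V4* lists 7,400 admission cultures. It derives 1,300 to 1,850 PCR tests from the "proportion (35 to 50 %) of admitted study patients fulfilling the screening test indication criteria". The admission screening section has all patients admitted to study wards swabbed within 24 h, except that previously recorded carriers are not PCR tested.

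**Current power claim.** Addendum 1 found a baseline incidence of 0.79% (95% CI 0.34% to 1.55%). It states that the planned sample size gives 80% power for a 50% reduction, at the upper confidence limit and allowing for clustering, only if the two hospitals are pooled.

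**The concern.** Swabs are taken on admission, before carriage or length of stay is known. The screened group therefore includes carriers and short stays, and the endpoint denominator excludes both. The protocol expects both kinds of patient: the intervention exists to find carriers on admission, and discharge surveillance is limited to stays over 48 h. One number cannot be the size of both groups.

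The 150% factor does not cover the gap, since the protocol assigns all of it to time dependence and clustering. At stake are the pooled power claim in Addendum 1 and the three-month interim check of whether there are enough subjects. That check has no defined target until the protocol says whether 7,400 counts admissions or at-risk stays.

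**Working it through.** **1. Reproduce 1,237.** Inputs from *Sample size estimate*: p1 = 0.03, p2 = 0.015, α = 0.05, power 0.80. Sidedness is not stated. With Poisson variance and a one-sided test:

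n = (1.645 + 0.842)² × (p1 + p2) / (p1 − p2)² = 6.183 × 0.045 / 0.000225 = 1,236.5, i.e. 1,237.

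This matches exactly. Two-sided versions give 1,534 (pooled normal) or 1,570 (Poisson) and do not match. The one-sided Poisson form is used below because it is the one that returns the plan's figure.

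**2. Slack.** 1,237 × 1.5 = 1,855.5, stated as 1,850, and 4 × 1,850 = 7,400. Conversely 1,850 / 1.5 = 1,233 against 1,237 required, so nothing is left over for carriers or short stays.

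**3. Which unit the other figures use.** 2 × 1,850 = 3,700 is the swab count in analysis E. In the budget, 0.35 × 3,700 = 1,295 and 0.50 × 3,700 = 1,850, which match its 1,300 to 1,850 tests, so 3,700 is there a count of admitted patients.

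**4. Addendum 1 claim.** Inputs: control 1.55% (upper confidence limit), intervention 0.775% (half of it), planned pooled arm 2 × 1,850 = 3,700. Addendum 1 gives no cluster factor, so 1.5 is carried over as an assumption.

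n = 6.183 × 0.02325 / 0.00775² = 2,393; 2,393 × 1.5 = 3,590.

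3,590 / 3,700 = 0.970. The claim holds if all 3,700 are at risk, and up to about 3% exclusions.

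**5. Power if 3,700 counts admissions.** Let f be the share of admissions in the endpoint denominator. The documents give no value, so f is an assumption. Effective n = 3,700 f / 1.5 and power = Φ(0.00775 / √(0.02325 / n) − 1.645).

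| f (assumed) | At-risk per arm | Effective n | Pooled power |
|---|---|---|---|
| 1.00 | 3,700 | 2,467 | 81.0% |
| 0.97 | 3,589 | 2,393 | 80.0% |
| 0.95 | 3,515 | 2,343 | 79.3% |
| 0.90 | 3,330 | 2,220 | 77.3% |
| 0.80 | 2,960 | 1,973 | 73.0% |
| 0.70 | 2,590 | 1,727 | 68.0% |

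**6. Sensitivity to the fixed factor.** If the 1.5 were all clustering, it would shrink with cluster size, roughly to 1 + 0.5 f. Effective n is then 3,330 / 1.45 = 2,297 at f = 0.90, 2,960 / 1.40 = 2,114 at 0.80 and 2,590 / 1.35 = 1,919 at 0.70. Power is 78.6%, 75.6% and 72.0%.

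**7. Admissions needed if 1,850 counts at-risk stays.** 1,850 / f per arm per hospital: 1,948 at f = 0.95, 2,056 at 0.90, 2,313 at 0.80, 2,643 at 0.70. Totals are 7,792, 8,224, 9,252 and 10,572. The swab and culture counts would then be too low.

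**The case against.** The strongest reply is that the design text means at-risk patients. *Study type and patient population* ties the 3% to the exposed population in the same sentence that gives 3,700 per hospital. The pass criteria under *Interim analysis and contingency plan* speak of at-risk admissions and an exposed denominator. On that reading the power is intact. The budget is weak evidence the other way: it is headed as still to be adjusted, and its 35 to 50% share reflects targeted screening, which *Ethical considerations* says was replaced by screening all admissions. This stands, and it is why the point cannot be that power is lost. It does not remove the conflict, because analysis E, without the budget, still gives 3,700 as the number of admission swabs.

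Second, the plan is not blind to size. Phases may be extended to 6 or 7 months if the pass criteria fail, and Addendum 1 adds a three-month check. These safeguards are real, but they need a defined unit to work against.

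Third, other matters weigh more on power. At the observed 0.79%, pooled one-sided power is about 56% even with all 3,700 per arm at risk, and the one-sided basis is undeclared. Both are separate issues. They leave no reserve for this one.

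**Conclusion.** The inconsistency is established. Under either reading a stated figure is wrong: the swab and culture counts if the number means at-risk stays, or the 80% power if it means admissions.

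A reader might infer that the trial does not have its stated power. The documents do not support that. They do not fix the unit, the design text leans towards at-risk patients, and no at-risk fraction is given. The size of any loss is therefore conditional: under 2 points from the computed 81% at f = 0.95, about 8 points at 0.80 and 13 at 0.70, and less if the design effect shrinks with cluster size. Nor does the admission-screening target of over 80% show that a fifth of patients drop out of the denominator. It is a floor, and Addendum 1 reports it as met without giving the rate.

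What is firm is the narrow margin of about 3% on the pooled claim. It assumes the one-sided formula that reproduces 1,237 and the 1.5 factor carried into Addendum 1. The per-hospital 80% at 3% versus 1.5% is not the claim to test, since Addendum 1 replaced it.

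**What to change.** - In *Sample size estimate* and Addendum 1, state whether 1,850, 3,700 and 7,400 are at-risk ward stays (at least 3 days, negative admission screen) or admissions.
- Take f from the baseline phase and report it. If the numbers are at-risk stays, give the matching admissions as 1,850 / f per arm per hospital. If 7,400 means admissions, restate the pooled power at 7,400 × f.
- Use the same unit in the three-month interim check of subject numbers.
- In secondary analysis E, replace N = 3,700 with the expected number of PCR-tested admissions, leaving out previously recorded carriers, who are not PCR tested.

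The cost is wording and one recalculation from data already collected. No added enrolment is required. The downside is that the stated power may become less favourable.
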